##### **8.4.2.1 Primary Efficacy Analyses**

The primary efficacy endpoint is the proportion of subjects with plasma HIV-1 RNA < 40 c/mL at the Week 24 snapshot. This endpoint is assessed with the FDA snapshot algorithm. The primary analysis will be based on a modified ITT (mITT) approach. A sensitivity analysis will be conducted using an observed values approach. The two approaches will be implemented as follows:

- Modified ITT: The numerator will be based on subjects with plasma HIV-1 RNA < 40 c/mL at Week 24. The denominator will be based on all treated subjects
- Observed values: Similar to the mITT approach, the numerator will be based on subjects with plasma HIV-1 RNA < 40 c/mL at Week 24. However, the denominator will be based on the treated subjects with plasma HIV-1 RNA at Week 24

Response rates will be tabulated by treatment arm with exact binomial 95% confidence intervals.

Subgroup summaries will be provided to examine the impact of baseline viral load and HIV-1 Clade AE (Clade AE versus Other) for both the mITT and the observed values approach. Other subgroup summaries may be provided to examine the impact of other important covariates such as CD4+ count, sex, geographic region, etc.

At Week 24, a Time to Loss of Virologic Response (TLOVR) analysis will be conducted as a sensitivity analysis that compliments the snapshot analysis. The following definition for virologic rebound will be used:

“For subjects that have been confirmed as having reached virologic suppression, by having two consecutive HIV-1 RNA readings below the assay limit of detection (40 copies/mL), virologic rebound is defined as confirmed HIV-1 RNA levels above the limit of detection. For levels above the limit of detection, confirmation consists of either two consecutive readings, or a single reading followed by loss to follow-up.”

#### **8.4.2.2 Secondary Efficacy Analyses**

The following secondary endpoints will be summarized by treatment arm:

- Proportion of subjects with HIV-1 RNA < 40 c/mL at Week 48 and Week 96 using mITT and observed values
- Proportion of subjects with HIV-1 RNA < 200 c/mL at Week 24, 48, and 96 using mITT and observed values
- Change from baseline in log10 HIV-1 RNA and in CD4+ T-cell counts, and changes in the percentage of CD4+ T-cells over time
- Newly emergent genotypic substitutions (using all on-treatment isolates) will be tabulated by treatment arm
- The newly emergent phenotypic resistance profile (using all on-treatment isolates) will be tabulated by treatment arm

#### **8.4.3 Safety Analyses**

The investigators will determine the intensity of adverse events (AEs) and the relationship of AEs to study therapy. The investigators' terms will be coded and grouped by system organ class using the latest version of the Medical Dictionary for Regulatory Activities (MedDRA) in production at BMS. AEs will be presented by system organ class and preferred term. Presentations will include both non-serious and serious adverse events, unless specified otherwise. If a subject had an adverse event with different intensities over time, then only the greatest intensity will be reported.

Deaths will be listed for enrolled subjects without regard to onset.

In analyses of fasting lipids over time, values will be excluded after the start of serum lipid reducing agents.

The frequency of the following safety events will be summarized by treatment arm for treated subjects:

- SAEs
- AEs leading to discontinuation of study therapy
- AEs by intensity
- CDC Class C AIDS events
- Laboratory abnormalities by toxicity grade

#### **8.4.4 Pharmacokinetic Analyses**

The following PK parameters will be summarized for BMS-955176, TDF and/or FTC by treatment arm:

- $C_{\max}$ : maximum observed plasma concentration
- $T_{\max}$ : time of maximum observed plasma concentration
- $C_{\text{tau}}$ : observed plasma concentration at the end of a dosing interval (eg, concentration at 24 hours)
- $C_0$ : observed pre-dose plasma concentration
- AUC(TAU) : area under the concentration-time curve in one dosing interval

##### **8.4.4.1 Sparse Pharmacokinetic Analyses**

Sparse pharmacokinetic data will be used in population PK, PK/PD and PK/VK analyses.

##### **8.4.4.2 PK/PD and PK/VK Analyses**

PK data obtained from this study will be pooled with data from other studies to perform an integrated population PK analysis, exposure-response analyses for selected safety and efficacy endpoints, and viral kinetic modeling of BMS-955176 in combination with other ARVs to support the on-going development of BMS-955176. These analyses will facilitate optimal dose selection for future Phase 3 studies.

The population PK, exposure-response, and viral kinetic analyses will be reported separately.

#### **8.4.5 Biomarker Analyses**

Not applicable.

#### **8.4.6 Outcomes Research Analyses**

Not applicable.

#### **8.4.7 Other Analyses (including Virologic Futility)**

Virologic Futility:

An analysis of virologic futility will be performed at Week 24. This analysis will be conducted to evaluate whether any BMS-955176 arm shows significantly worse antiviral efficacy (HIV-1 RNA < 40 c/mL using the FDA snapshot algorithm) than the EFV containing arm. The comparison of Arms 1-3 (containing BMS-955176) to Arm 4 (containing EFV) will be made with one-sided, Fisher's exact tests, conducted at the 0.01 probability level.

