Subjects in this clinical study will benefit from receiving cART potentially containing BMS-955176. Preliminary data from the Phase 2a (Part A, B, and C) study show a maximum median reduction in HIV-1 RNA (clades B and C) ranging from 1.3 to 1.7 log10 in the dose arms estimated to provide similar exposure to those in this current study. When BMS-955176 was combined with ATV ± RTV (Part B) this resulted in maximum median declines in HIV-1 RNA ranging from 1.9 to 2.2 log10. These results are generally similar to the antiviral effect demonstrated by other classes of ARVs. Thus, BMS-955176 should contribute with other ARVs substantially to form an effective cART regimen.

As with any antiretroviral study in HIV-1-infected subjects, there is a risk for the development of treatment failure and the development of drug resistance associated mutations to BMS-955176 and/or other antiretrovirals. However, drug resistance to the maturation inhibitor would not be anticipated to result in cross-resistance to any other ARV class, including protease inhibitors. Ongoing analysis of preliminary data from the Phase 2a study is evaluating both emergent genotypic and phenotypic changes after short term monotherapy with BMS-955176. The use of three fully susceptible agents as a part of cART is expected to decrease the probability of virologic failure and drug resistance. Initially in this clinical trial, measurement of HIV-1 RNA will occur more frequently than in standard clinical practice which will allow for increased vigilance for the development of lack of efficacy/resistance. Finally, an analysis for virologic futility will occur at Week 24 (see [Section 8.4.7](#)).

In-vitro studies show that BMS-955176 is expected to be active against a variety of HIV-1 clades albeit with EC50s approximately 2-3 fold less toward HIV-1 clade AE compared to clade B (see [Section 1.4.1](#)). As described in [Section 1.1.1](#), the only clinical data for BMS-955176 exists in HIV-1 clade B and C. The efficacy profile of BMS-955176 in other HIV-1 clades encountered in other geographical regions where this multinational Phase 2b trial will be conducted (eg, clade AE in Thailand) is unknown. To mitigate the risk of randomizing subjects infected with HIV-1 with an unknown efficacy profile, this clinical trial will randomize a maximum of ~ 8% of total subjects (n = 16) who are infected with HIV-1 clade AE.

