### **3 INVESTIGATIONAL PLAN**

#### **3.1 Study Design and Duration**

This is a randomized, active-controlled, double-blind clinical trial. Approximately 200 treatment-naïve HIV-1 infected subjects will be randomized 1:1:1:1 to one of four treatment arms (approximately 50 per arm) with the resulting drugs/doses as follows:

- Arm 1: BMS-955176 60 mg QD + TDF/FTC 300/200 mg QD, or
- Arm 2: BMS-955176 120 mg QD + TDF/FTC 300/200 mg QD, or
- Arm 3: BMS-955176 180 mg QD + TDF/FTC 300/200 mg QD, or
- Arm 4: EFV 600 mg QD + TDF/FTC 300/200 mg QD

Randomization will be stratified by HIV-1 Clade (AE versus Other). The number of subjects with HIV-1 Clade AE will be capped at a maximum of approximately 16 total, approximately 4 per treatment arm.

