## **8 STATISTICAL CONSIDERATIONS**

### **8.1 Sample Size Determination**

This is an estimation study, without statistical testing, and hence there are no power considerations.

It is expected that the response rate for the primary endpoint will be somewhere around 80%. With this response rate, and 50 subjects per arm, an exact 95% confidence interval would run from roughly 66% to 90%.

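### The protocol declares no testing and no power considerations, yet a Fisher test at 0.01 drives an arm-wide dose change and is more likely than not to miss a 20-point deficit

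*Protocol*

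**What the plan says.** Protocol Section 8.1 states: "This is an estimation study, without statistical testing, and hence there are no power considerations". The synopsis repeats this. The only design figure given is the precision of one arm's response rate: at about 80% response and 50 subjects, an exact 95% interval of roughly 66% to 90%.

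Section 8.4.7 sets out a Week 24 analysis asking if one of the dose arms "shows significantly worse antiviral efficacy (HIV-1 RNA < 40 c/mL using the FDA snapshot algorithm) than the EFV containing arm". Each dose arm is set against Arm 4 by one-sided Fisher's "exact tests, conducted at the 0.01 probability level". That makes three tests against a shared control. No detection probability is given, and Section 8.4.7 names the snapshot algorithm without a denominator. For the primary snapshot analysis, Section 8.4.2.1 says: "The denominator will be based on all treated subjects".

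Two other sections rely on the result. Under Section 3.1.5, subjects in an arm that meets the criterion move to the next dose up that remains available. Section 1.5 closes its account of how the risk of treatment failure and resistance is limited with: "Finally, an analysis for virologic futility will occur at Week 24".

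**The concern.** A test with a fixed significance level and a treatment consequence is a decision rule, and a decision rule has error rates whether or not they are stated. The protocol does more than leave them to a later document: it says that no testing takes place, so the question of sensitivity never arises.

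What is at stake is how a negative result will be read. If an arm does not trigger, investigators and ethics committees who have read Section 1.5 may take that as evidence that the arm is performing adequately. With 50 per arm and a one-sided level of 0.01, that reading is justified only for very large deficits.

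**Working it through.** **Inputs from the protocol.** About 50 per arm, allocated 1:1:1:1 (Section 3.1); response about 80% on the snapshot endpoint (Section 8.1); one-sided Fisher's exact test at 0.01, each of Arms 1-3 against Arm 4 (Section 8.4.7). **Assumed:** EFV responds at the expected 80%, varied from 75% to 90%, and the size of the true deficit. The protocol names no target deficit.

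**Step 1: the plan's own figure.** Clopper-Pearson interval for 40/50: lower limit = Beta(0.025; 40, 11) = 0.663; upper limit = Beta(0.975; 41, 10) = 0.900. The stated 66% to 90% is reproduced.

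**Step 2: where the rule triggers.** With c responders of 50 on EFV and t of 50 on the arm, the one-sided p-value is the lower hypergeometric tail, p(c,t) = sum over k ≤ t of C(50,k)·C(50,c+t−k)/C(100,c+t).

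- 40 vs 28: p = 0.0088, triggers.
- 40 vs 29: p = 0.0149, does not.

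Against EFV 40/50 the arm must be at 28/50 (56%) or lower, an observed deficit of 80 − 56 = 24 points.

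**Step 3: detection probability.** Power = sum over all c, t of Bin(c; 50, pE)·Bin(t; 50, pA), counted where p(c,t) ≤ 0.01. With pE = 0.80:

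| True arm rate | Deficit (points) | Fisher at 0.01 | Boschloo at 0.01 |
|---|---|---|---|
| 70% | 10 | 8.4% | 10.0% |
| 65% | 15 | 20.1% | 23.1% |
| 60% | 20 | 37.5% | 41.6% |
| 55% | 25 | 57.4% | 61.8% |
| 50% | 30 | 75.4% | 79.2% |
| 40% | 40 | 95.5% | not needed |

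For a 20-point deficit, Fisher's power is 34% if EFV is 75%, 42% if 85% and 49% if 90%. It stays below one half throughout.

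**Step 4: true size.** With equal rates, the same sum gives 0.0052 per comparison at 80% and about 0.006 at its maximum over all common rates, so Fisher uses little more than half of the nominal 0.01. Boschloo's test uses the Fisher p-value as its statistic and rejects at p ≤ 0.0136. Its maximum size is 0.0098, still below 0.01. With three arms at 80%, the chance of any false trigger is 1.4% with Fisher and 1.8% with Boschloo.

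**The case against.** The rule was plausibly meant to catch gross failure with few false triggers, and it does that: 75% at 30 points, 88% at 35 and 96% at 40. A 20-point benchmark is the reader's choice. No figure in the protocol is arithmetically wrong. All of this stands, but none of it makes the statement about testing and power correct.

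Three stronger readings are tempting, and the documents do not support them.

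- *The rule will miss a virologically failing arm.* It misses a 20-point deficit about 62% of the time (100 − 37.5), but finds very large deficits reliably.
- *It is the only protection for subjects on a weak arm.* Section 3.5 requires individual discontinuation for emergent resistance and for confirmed viral load above set thresholds after Weeks 24 and 48. Section 5.4.1.1 adds confirmatory and resistance testing. Section 3.1.5 selects a Continuation Dose from all the Week 24 data. It remains true that the test is the only pre-specified arm-level comparison with a threshold, that Section 7 provides no monitoring committee, and that before Week 24 the viral-load management in Section 5.4.1.1 is partly discretionary.
- *EFV dropouts lower the bar and hide virologic failure.* On an all-treated denominator, snapshot non-response includes non-virologic dropout in every arm. It masks failure only if EFV loses more subjects than the BMS-955176 arm. The protocol describes EFV side effects in Section 1.4.2 and potential gastrointestinal toxicity of BMS-955176 in Section 1.5, and gives no dropout rate for either. An assumed split of response/virologic failure/other of 80/4/16 on EFV and 70/24/6 on the arm gives 8% for the snapshot test and 66% for a Fisher test on virologic failure. That 66% falls to 49%, 35% and 24% if EFV failure is 6%, 8% or 10%. Reversing the imbalance (80/14/6 against 60/24/16) gives 38% for the snapshot test and only 10% for the failure test. The 80% expectation is also for the snapshot endpoint and already includes dropout, so masking must not be added on top of the 38%.

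**Conclusion.** The point holds as a wrong statement together with undisclosed operating characteristics. The protocol contains three formal tests with a treatment consequence, contrary to Section 8.1 and the synopsis. Under the protocol's own inputs the rule is more likely than not to miss a true 20-point deficit: power 38% at EFV 80%, and 34% to 49% for EFV rates of 75% to 90%. Failing to trigger is therefore weak evidence that an arm is adequate. The size rests on 50 evaluable per arm and on deficits that are assumptions, not protocol targets. The documents do not establish that the snapshot endpoint biases the test in favour of BMS-955176, or that subjects are otherwise unprotected.

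**What to change.** 1. Correct Section 8.1 and the synopsis: the primary aim is estimation, but one futility rule is tested. State its detection probabilities (8%, 20%, 38%, 75% and 96% for 10, 15, 20, 30 and 40 points at EFV 80%), label the deficits as assumptions, and name the denominator in Section 8.4.7.
2. Replace Fisher by Boschloo's exact test at the same 0.01 level. The gain is modest: 42% at 20 points and 79% at 30. The boundary against EFV 40/50 does not move, because 0.0149 exceeds the cut of 0.0136. The cost is a slightly higher true false-trigger rate, still below 0.01.
3. Report each arm-minus-EFV difference with a 95% confidence interval, so that a non-trigger is not read as adequacy.
4. Beside the snapshot test, show a comparison of virologic failure (HIV-1 RNA ≥40 c/mL in the window, or stopped for virologic reasons). Keep it supportive: as the trigger it could be more or less sensitive, depending on which arm loses more subjects.

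The cost is wording in Sections 8.1 and 8.4.7 and the synopsis, a few lines of code, and openly disclosing modest power. No subjects are added, and the dose consequence in Section 3.1.5 is untouched.

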## **8.5 Interim Analyses**

An interim analysis will be conducted when approximately 50% of the subjects have completed 24 weeks of therapy. Access to the unblinded data will be restricted to a limited number of BMS and vendor personnel involved in the development of models for population pharmacokinetics, exposure-response relationships, and viral kinetics.

An interim analysis will be conducted after the last randomized subject is on study therapy for 24 weeks.

An interim analysis will be conducted after the last randomized subject is on study therapy for 48 weeks.

The final analysis will be conducted after the last randomized subject is on study therapy for 96 weeks.

## **9 STUDY MANAGEMENT**

### **9.1 Compliance**

#### **9.1.1 *Compliance with the Protocol and Protocol Revisions***

The study shall be conducted as described in this approved protocol. All revisions to the protocol must be discussed with, and be prepared by, BMS. The investigator should not implement any deviation or change to the protocol without prior review and documented approval/favorable opinion from the IRB/IEC of an amendment, except where necessary to eliminate an immediate hazard(s) to study subjects.

If a deviation or change to a protocol is implemented to eliminate an immediate hazard(s) prior to obtaining IRB/IEC approval/favorable opinion, as soon as possible the deviation or change will be submitted to:

- IRB/IEC for review and approval/favorable opinion
- BMS
- Regulatory Authority(ies), if required by local regulations

Documentation of approval signed by the chairperson or designee of the IRB(s)/IEC(s) must be sent to BMS.

If an amendment substantially alters the study design or increases the potential risk to the subject: (1) the consent form must be revised and submitted to the IRB(s)/IEC(s) for review and approval/favorable opinion; (2) the revised form must be used to obtain consent from subjects currently enrolled in the study if they are affected by the amendment; and (3) the new form must be used to obtain consent from new subjects prior to enrollment.

If the revision is done via an administrative letter, investigators must inform their IRB(s)/IEC(s).

### **9.1.2      *Monitoring***

BMS representatives will review data centrally to identify potential issues to determine a schedule of on-site visits for targeted review of study records.

Representatives of BMS must be allowed to visit all study site locations periodically to assess the data quality and study integrity. On site they will review study records and directly compare them with source documents, discuss the conduct of the study with the investigator, and verify that the facilities remain acceptable. Certain CRF pages and/or electronic files may serve as the source documents:

In addition, the study may be evaluated by BMS internal auditors and government inspectors who must be allowed access to CRFs, source documents, other study files, and study facilities. BMS audit reports will be kept confidential.

The investigator must notify BMS promptly of any inspections scheduled by regulatory authorities, and promptly forward copies of inspection reports to BMS.

#### **9.1.2.1      *Source Documentation***

The Investigator is responsible for ensuring that the source data are accurate, legible, contemporaneous, original and attributable, whether the data are hand-written on paper or entered electronically. If source data are created (first entered), modified, maintained, archived, retrieved, or transmitted electronically via computerized systems (and/or any other kind of electronic devices) as part of regulated clinical trial activities, such systems must be compliant with all applicable laws and regulations governing use of electronic records and/or electronic signatures. Such systems may include, but are not limited to, electronic medical/health records (EMRs/EHRs), adverse event tracking/reporting, protocol required assessments, and/or drug accountability records).

When paper records from such systems are used in place of electronic format to perform regulated activities, such paper records should be certified copies. A certified copy consists of a copy of original information that has been verified, as indicated by a dated signature, as an exact copy having all of the same attributes and information as the original.

### **9.1.3      *Investigational Site Training***

Bristol-Myers Squibb will provide quality investigational staff training prior to study initiation. Training topics will include but are not limited to: GCP, AE reporting, study details and procedure, electronic CRFs, study documentation, informed consent, and enrollment of WOCBP.

## **9.2          *Records***

### **9.2.1      *Records Retention***

The investigator must retain all study records and source documents for the maximum period required by applicable regulations and guidelines, or institution procedures, or for the period

specified by BMS, whichever is longer. The investigator must contact BMS prior to destroying any records associated with the study.

BMS will notify the investigator when the study records are no longer needed.

If the investigator withdraws from the study (eg, relocation, retirement), the records shall be transferred to a mutually agreed upon designee (eg, another investigator, IRB). Notice of such transfer will be given in writing to BMS.

### **9.2.2 Study Drug Records**

It is the responsibility of the investigator to ensure that a current disposition record of study drug (inventoried and dispensed) is maintained at the study site to include the investigational product and the non-investigational product(s). Records or logs must comply with applicable regulations and guidelines and should include:

- amount received and placed in storage area
- amount currently in storage area
- label identification number or batch number
- amount dispensed to and returned by each subject, including unique subject identifiers
- amount transferred to another area/site for dispensing or storage
- nonstudy disposition (eg, lost, wasted)
- amount destroyed at study site, if applicable
- amount returned to BMS
- retain samples for bioavailability/bioequivalence, if applicable
- dates and initials of person responsible for Investigational Product dispensing/accountability, as per the Delegation of Authority Form

BMS will provide forms to facilitate inventory control if the investigational site does not have an established system that meets these requirements.

### **9.2.3 Case Report Forms**

An investigator is required to prepare and maintain adequate and accurate case histories designed to record all observations and other data pertinent to the investigation on each individual treated or entered as a control in the investigation. Data that are derived from source documents and reported on the CRF must be consistent with the source documents or the discrepancies must be explained. Additional clinical information may be collected and analyzed in an effort to enhance understanding of product safety. CRFs may be requested for AEs and/or laboratory abnormalities that are reported or identified during the course of the study.

For sites using the BMS electronic data capture tool, electronic CRFs will be prepared for all data collection fields except for fields specific to SAEs and pregnancy, which will be reported on the paper or electronic SAE form and Pregnancy Surveillance form, respectively. Spaces may be

left blank only in those circumstances permitted by study-specific CRF completion guidelines provided by BMS.

The confidentiality of records that could identify subjects must be protected, respecting the privacy and confidentiality rules in accordance with the applicable regulatory requirement(s).

The investigator will maintain a signature sheet to document signatures and initials of all persons authorized to make entries and/or corrections on CRFs.

The completed CRF, including any paper or electronic SAE/pregnancy CRFs, must be promptly reviewed, signed, and dated by the investigator or qualified physician who is a subinvestigator and who is delegated this task on the Delegation of Authority Form. For electronic CRFs, review and approval/signature is completed electronically through the BMS electronic data capture tool. The investigator must retain a copy of the CRFs including records of the changes and corrections.

Each individual electronically signing electronic CRFs must meet BMS training requirements and must only access the BMS electronic data capture tool using the unique user account provided by BMS. User accounts are not to be shared or reassigned to other individuals.

